### 2.4. Statistical Analysis

#### 2.4.1. Sample Size

According to the results of the study by Negut, Jurma and David [35], who evaluated the attention in children with ADHD using an AULA VR (virtual reality classroom) system, the minimum standardized difference (d/s, where d = difference between neurotypical and clinical groups; s = standard deviation of the neurotypical group) that could be considered clinically relevant is one point. According to this value, for a bilateral contrast with α = 0.05, and a power of 1-β = 0.90, the initially estimated sample size is 21 children. Taking into account the possible losses during the evaluation, the sample size will be increased by 20%, thus, the estimated final sample size is 26 children with neurodevelopmental disorders.

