#### 1.1.2. Hypotheses

Ten sessions of “SR-MRehab: Un colegio emocionante” involving VR will have the same effects as the standard program on the improvement of self-regulation.

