## 4. Conclusions

The present study will provide data on the effectiveness and acceptability of the “SR-MRehab: Un colegio emocionante” intervention, as well as data from feasibility trials to provide information about the design and sample size for a large-scale trial. In addition, based on the experiences of the participants in the intervention, qualitative data will be obtained to determine the feasibility of the MRehab tool [25,41], to design and perform these rehabilitation activities in a school setting.

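### The 1-SD target behind the 90% power is a neurotypical-versus-clinical difference on attention and is not justified as a difference between the VR and standard programmes

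*Protocol article*

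**What the plan says.** Section 2.4.1 relies on a cited study "who evaluated the attention in children with ADHD using an AULA VR (virtual reality classroom) system". It takes from that study the minimum standardised difference "that could be considered clinically relevant is one point", and defines the ratio with "d = difference between neurotypical and clinical groups; s = standard deviation of the neurotypical group". The calculation is then run "for a bilateral contrast with α = 0.05, and a power of 1-β = 0.90", and "the initially estimated sample size is 21 children". A 20% allowance for losses brings this to 26. Neither figure is said to be per group, so both read as totals.

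The comparison the trial makes is described elsewhere in the article:

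- Sections 1.1.1 and 2.1 compare the VR programme with a standard self-regulation programme. Both run for ten weekly sessions, and no neurotypical group is randomised.
- Section 2.2.3 (Control Group) describes the control activities as similar to the experimental ones but without VR. Table 3 largely mirrors Table 2.
- Section 2.2.4 names emotional regulation as the primary outcome, measured by the NEPSY-II Affect Recognition errors and the Theory of Mind score.
- Section 1.1.2 expects that the VR programme "will have the same effects as the standard program on the improvement of self-regulation".
- Section 4 says the study will also supply "data from feasibility trials to provide information about the design and sample size for a large-scale trial".

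**The concern.** A target difference for a two-arm trial should be a difference between the two arms, on the primary outcome, in the units of variation found in the trial population. The one used here is defined on three other terms:

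- the contrast is between diagnostic groups, not between programmes;
- the scaling SD is that of neurotypical children, not of the children who will be randomised;
- the source outcome is attention, not affect recognition or theory of mind.

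The distance between clinical and neurotypical children does not show how far apart two similar active programmes might end up, or what difference between them would matter.

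What is at stake is how the result is read. Section 2.4.2 plans difference tests at p < 0.05, and the hypothesis is that the programmes have the same effects. With a stated power of 90%, a non-significant result could be taken as support for that hypothesis, although the data might still be compatible with a sizeable difference.

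**Working it through.** **Inputs from section 2.4.1.** Standardised difference 1.0; two-sided α 0.05; power 0.90; 21 children before losses; 26 after. Equal allocation is assumed, because section 2.2 states simple randomisation without a ratio.

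**Reproducing the plan's figure.** For two means, n per arm = 2(z₀.₉₇₅ + z₀.₉₀)²/d² = 2(1.960 + 1.282)²/1² = 21.01. The exact t-test needs 23 per arm to exceed 0.90; 22 gives 0.900 after rounding, and 21 gives 0.885. So 21 is reproduced, but as a per-arm number; the two-arm total would be 42 to 46. For losses, 21/(1 − 0.20) = 26.25 and 21 × 1.20 = 25.2, both in line with 26.

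The arithmetic therefore shows only this: *if* the two compared groups differ by 1 SD and each has about 21 to 23 children, power is about 0.90. The input of 1 SD is the part without support.

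**How power depends on that input.** The article gives no between-programme effect and no SD for a primary outcome, so no corrected sample size can be derived. The values 0.8, 0.5 and 0.3 SD below are an assumed range. Power is from the noncentral t, two-sided 0.05, with noncentrality d·√(n₁n₂/(n₁+n₂)). Both readings of 26 are shown.

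| True difference | 26 in total (13 v 13) | 26 per arm |
|---|---|---|
| 1.0 SD | 0.69 | 0.94 |
| 0.8 SD | 0.50 | 0.81 |
| 0.5 SD | 0.23 | 0.42 |
| 0.3 SD | 0.11 | 0.19 |

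The fall *down* each column is the effect of the unsupported target. The gap *between* the columns, including 0.69 against 0.94 at 1.0 SD, comes only from the per-arm or total question and is a separate matter.

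**Precision, which needs no target effect.** The 95% CI half-width in SD units is t₀.₉₇₅,df × √(1/n₁ + 1/n₂).

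- 13 v 13: 2.064 × 0.392 = 0.81 SD; detectable difference at 80% power 1.15 SD.
- 11 v 10 (21 completers in total): 2.093 × 0.437 = 0.91 SD; detectable difference 1.29 SD.
- 26 v 26: 2.009 × 0.277 = 0.56 SD; detectable difference 0.79 SD.

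**Population SD.** If the SD among the trial's children were 1.25 or 1.5 times the neurotypical SD (an assumption), the same raw difference would be 0.80 or 0.67 SD in the trial population. Power with 21 per arm would then be 0.72 or 0.56 instead of 0.885.

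**The case against.** The best defence is that section 2.4.1 calls 1 SD the minimum relevant difference, not the expected one. A target difference need not be what investigators expect, so the same-effects hypothesis does not by itself refute it. Power at a fixed standardised difference of 1 is also a valid conditional statement, and no raw neurotypical SD enters the formula. This stands, and it limits the point to one of justification: a relevance threshold still has to be argued for the comparison being made, and the article defines it only for another one.

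A reader might go further and infer that the trial could not detect any plausible difference. The document does not support that. The range 0.3 to 0.8 SD is assumed, no figure in the article shows 1 SD to be implausible, and with 26 per arm power at 0.8 SD would be 0.81.

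A reader might also infer that the construct is wholly foreign to the trial. That is too strong, since attention belongs to the secondary outcome under Cognitive Flexibility and appears as executive attention in Table 1. The valid statement is that it is not the primary outcome.

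Finally, no sentence in the article says that p > 0.05 will be read as sameness. Section 2.4.2 already plans 95% CIs and effect sizes, and section 4 already mentions feasibility. The misreading is a risk that the wording leaves open, not a stated plan.

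**Conclusion.** The point holds as one of unsupported justification. The statement of "a power of 1-β = 0.90" is true only for a real 1-SD difference between the programmes with about 21 to 23 children per arm. The article gives no reason to treat 1 SD as the smallest difference between these two programmes worth detecting on Affect Recognition or Theory of Mind, so the figure does not show that the trial can detect a relevant difference.

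At an assumed 0.5 SD, power is between 0.23 and 0.42 depending on what 26 means. A confidence interval would extend about 0.6 to 0.8 SD either side of the estimate with all children analysed, and about 0.9 SD with 21 completers in total. These figures assume equal arms and an unadjusted two-sample t-test; baseline adjustment, which section 2.4.2 plans only if needed, could improve them somewhat. Settling the per-arm question alone would not resolve the point, because the target would remain unjustified.

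**What to change.** In section 2.4.1:

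1. Remove the neurotypical-versus-clinical difference as the basis for the target, and drop the unqualified 90% power claim.
2. State whether 26 is the total or the number per arm.
3. Give the precision that matches that answer. For 26 in total: half-width 0.81 SD and detectable difference 1.15 SD at 80% power (0.91 and 1.29 SD with 21 completers). For 26 per arm: 0.56 and 0.79 SD. If power is shown, show it over a range of differences and label that range as assumed.
4. Describe the trial as providing estimates with 95% CIs to inform a larger trial, in line with section 4, and state that p > 0.05 will not be taken to show that the programmes have the same effect.

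The cost is wording only, and this restatement needs no extra children. The downside is a less favourable stated power. The figures in step 3 should not be printed until step 2 is settled, since the wrong set would misstate the precision.

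### The 21 children in section 2.4.1 fit the stated inputs as a per-arm number but are not labelled so; if 26 is the trial total, power at 1 SD is about 56–69%, not 90%

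*Protocol article*

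**What the plan says.** Section 2.4.1 (Sample Size) takes its effect size from a study of attention in children with ADHD that used a virtual-reality classroom. The smallest standardised difference "that could be considered clinically relevant is one point", with "d = difference between neurotypical and clinical groups; s = standard deviation of the neurotypical group". The test is specified as "for a bilateral contrast with α = 0.05" with "a power of 1-β = 0.90". From these inputs, "the initially estimated sample size is 21 children". After a 20% increase for losses, "the estimated final sample size is 26 children with neurodevelopmental disorders".

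Neither 21 nor 26 is described as per arm or as a total. Sections 2.1 and 2.2 describe one pool of children allocated to an experimental or a control group by simple randomisation, and give no arm sizes. Section 2.4.2 compares groups with Student's t, Mann–Whitney, ANOVA or Kruskal–Wallis tests. Regression adjustment is used only if needed, for covariates that differ at baseline and correlate with the result.

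**The concern.** A final sample size given without qualification is normally read as the number of children in the trial. On that reading the per-arm result of a two-group formula has been used for the whole trial, which then has half the children its own calculation requires. The stated 90% power would be wrong.

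This matters more than usual here because section 1.1.2 hypothesises that the virtual-reality programme will do as well as the standard one. A non-significant difference could easily be taken as support for that hypothesis, and a claimed 90% power would lend weight to that reading. If the true power is well below 90%, a non-significant result says much less.

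The effect size raises a second question. The 1-SD figure is defined between neurotypical and clinical children in a study of attention. The trial compares two active programmes, both given to children with special educational needs, and its primary outcomes in section 2.2.4 are the Affect Recognition and Theory of Mind subtests.

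**Working it through.** **Inputs (section 2.4.1):** standardised difference d = 1; two-sided alpha 0.05 (z = 1.960); power 0.90 (z = 1.282); 20% increase for losses. Two arms come from section 2.1. A 1:1 ratio is assumed, since none is stated.

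**Reproducing 21**
- Two-group normal formula: n per arm = 2 × (1.960 + 1.282)² / 1² = 21.01. This matches the stated 21, as a per-arm number.
- Exact two-sample t-test: 22 per arm gives 89.97% power and 23 gives 91.2%, so 23 per arm are needed.
- One-sample or paired comparison: (1.960 + 1.282)² = 10.5, so 11; by the t-test, 13. Neither is 21.

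**Reproducing 26:** 21 × 1.2 = 25.2, rounded up to 26. This follows the section's own rule.

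**Could 21 be a two-arm total?** That needs the variance halved. With baseline adjustment, 1 − r² = 0.5, so r ≈ 0.71. With change scores, 2(1 − r) = 0.5, so r = 0.75. The article states neither correlation and mentions no such adjustment in the calculation.

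**Power at d = 1 if 26 is the total** (two-sided t-test; noncentrality = d × √[n₁n₂/(n₁ + n₂)])

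| Evaluable children | Noncentrality | Power, t-test | Power, normal approximation |
|---|---|---|---|
| 13 + 13 (no losses) | √6.5 = 2.55 | 68.7% | 72.2% |
| 10 + 11 (planned loss) | √(110/21) = 2.29 | 58.4% | 62.9% |
| 10 + 10 (planned loss) | √5 = 2.24 | 56.2% | 60.9% |

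The planned loss leaves 26 × 0.8 = 20.8 children, hence 20 or 21. Simple randomisation can also produce unequal arms: 9 + 17 with no losses gives 64.4%.

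**Difference detectable with 90% power:** about 1.33 SD with 13 + 13 and about 1.49 SD with 10 + 11.

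**Width of the 95% confidence interval** (half-width in SD units, t × √(1/n₁ + 1/n₂)): 2.064 × √(2/13) = 0.81 with 13 + 13; 2.093 × √(1/10 + 1/11) = 0.91 with 10 + 11.

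**If 26 per arm was meant:** 21 + 21 evaluable children give 88.5% power by the t-test and 90.0% by the normal approximation. The total randomised would be 2 × 26 = 52.

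**The case against.** The strongest objection is that the article never says that 26 is the total. It gives no arm sizes and no allocation total. If 26 per arm was intended, the calculation is about right and only the label is missing. This stands. The loss of power is therefore conditional on the total reading. What is certain is that the figures carry no label that fits the inputs. The objection does not clear the section, because the number of children in the trial would then be 52, which appears nowhere.

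It is also fair to say that a total of 21 is not impossible: a strong enough baseline correlation would produce it. But section 2.4.1 does not use one, and the adjustment in section 2.4.2 is contingent.

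One could add that the trial has a feasibility purpose, since section 4 expects "data from feasibility trials to provide information about the design and sample size for a large-scale trial". That may justify a small trial. It does not justify stating 90% power for one.

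A reader might infer two stronger points, which the article does not support:
- *The loss allowance is wrong.* Dividing by 0.8 gives 26.25, or 27 rounded up. But the section says the number is increased by 20%, and 26 follows from that. The choice between the two is a convention, and the difference is one child.
- *One SD would require the programme to normalise the children completely.* Section 2.4.1 calls 1 the smallest relevant difference. It does not say that the observed gap between neurotypical and clinical children was 1 SD, and the cited study is not at hand. The text supports only the narrower point that the benchmark concerns a different contrast and a different outcome.

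**Conclusion.** The point holds in conditional form. The inputs of section 2.4.1 yield 21 as a per-arm number under the standard two-group formula, and nothing stated in the article turns it into a total. On the plain reading that 26 is the whole trial, power at 1 SD is about 69% without losses and about 56–58% after the planned loss. The chance of missing a true 1-SD difference is then 31–44%, against the stated 10%. The normal approximation is slightly kinder (61–72%) but leads to the same conclusion.

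These figures assume a 1:1 split, an unadjusted two-sided t-test and d = 1. On the other reading, 26 per arm, the power claim is roughly right and the trial size is understated by half. Section 2.4.1 needs correcting on either reading.

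The 1-SD input is an assumption. The article gives no argument linking a neurotypical-versus-clinical benchmark on attention to the expected difference between two active programmes on the primary outcomes.

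**What to change.** In section 2.4.1:
1. State whether 21 and 26 are per arm or total.
2. If 26 is the total, replace the 90% with about 69% power without losses and about 58% with the planned 20% loss. Alternatively, keep 90% and restate the detectable difference as 1.3–1.5 SD.
3. If 26 per arm was meant, state the total as 52.
4. Say that d = 1 is an assumption taken from a neurotypical-versus-clinical benchmark on attention, not the difference expected between the two programmes on the primary outcomes.

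If 26 is the total, the cost is a few sentences and a less favourable power figure; no extra children are needed. If 52 was always intended, only the wording changes. Enlarging a trial planned at 26 would not be cheap and is not part of this fix.

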#### 2.4.2. Data Analysis Plan

A descriptive analysis will be carried out for all the variables in the study. The qualitative variables will be described with absolute frequencies and percentages for each of their categories, and quantitative variables with mean, standard deviation (DE), maximum and minimum values, as well as median and interquartile range, where appropriate. The corresponding 95% confidence intervals (ICs) will be calculated. The normality of the continuous variables will be verified using graphical methods and normality tests.

The Chi-square test will be used to study the statistical significance of the differences between proportions. To study the statistical significance of the differences between means, different tests, questionnaire scores, completion time and number of errors of each virtual task throughout the different sessions, the following tests will be used depending on whether or not the variables to be compared show normality: Student’s t test, Mann–Whitney U-test, ANOVA or Kruskal–Wallis test. Furthermore, the effect size of the changes observed will also be calculated. The analysis of the association between two quantitative variables will be performed, using Pearson’s or Spearman’s correlation coefficient, depending on whether or not the variables show normality.

If necessary, generalized linear regression models will be used to adjust the results for any confounding covariate that shows significant baseline differences between the groups and a correlation with the result. For the hypothesis testing, a significance level of 5% will be assumed (*p* < 0.05). All statistical analyses will be carried out using the IBM SPSS software (version 24, IBM Corporation, New York, NY, USA).

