#### 2.2.1. Study Variables 

The main variables of the study can be divided into two main dimensions: (1) cognitive regulation or executive functions: inhibitory control, flexibility, planning, reasoning, and problem solving; (2) emotional regulation: emotional perception and emotional regulation. These variables were, and will be, evaluated through several questionnaires provided to parents, teachers and students and tests performed by children, as shown in Table 1.

Additionally, other sociodemographic data and information about the child’s development and learning history will be collected. Through the “SR-MRehab: Un colegio emocionante”, in each session, the following information will be collected for each task: number of hits, cognitive errors, and the time required by each participant to complete the task.

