#### 2.2.3. Intervention

##### Experimental Group 

The intervention on self-regulation will be carried out through a non-immersive virtual reality platform, “SR-MRehab: Un colegio emocionante”, in which the participants must conduct a series of activities designed specifically for this purpose. These activities will be performed by the children using mainly their hands to manage the virtual objects shown in the screen. To this end, our system makes use of a Kinect motion sensor connected to the computer, to control the body movements of the child. Moreover, our system records some relevant data of the execution of these activities for further analysis of the child’s performance.

The tasks will be divided into two blocks: emotional regulation (ER) and cognitive regulation (CR) (or executive functions), in a total of 10 sessions, once a week, performing a task of each block per session. Each session will last 50 min and will generally take into account the development of the different executive functions (working memory, inhibitory control, flexibility, reasoning, planning and problem solving) [15] and emotional competencies (emotional perception, and emotional self-regulation) [48]. Table 2 and Table 3 show the organization, description and aims of each session for the Experimental and Control Group, respectively. These sessions will take place from January to April 2021.

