The principles of the program will be based on the following premises for children with ASD [7,49]: (1) strengthening communicative attempts; (2) choosing the most natural contexts possible; (3) establishing structured and predictable routines and environments; (4) visually supporting information; and (5) adapting our language to the understanding level of the child. Regarding the difficulty of interpreting and responding to social emotions and cues, perspective games are of great interest, where the child and the therapist describe the same object from different perspectives, as well as guessing games (guess what is in this box) and games with social stories, which are short stories that use pictograms to help understand situations with social ambiguity: (1) describing what happens; (2) orienting the action, indicating the child what to do in that situation; (3) anticipating and explaining what can happen and how the child can feel; and (4) developing a strategy that can be applied in similar situations. Virtual stories narrated with puppets can be used in young children. In older children, training techniques may also be used in social skills, with role-playing, theatre, or body expression groups. These activities can be very helpful in teaching skills to predict people’s most likely behavior in certain situations, explaining how people feel, recognizing emotions of joy, sadness, fear, anger, etc., predicting those emotions based on the situation, understanding that emotions depend on desires and beliefs, and assuming someone else’s perspective, which may not match one’s own perspective.

Regarding the executive functions, the proposed activities are intended for the children to notice and detect small changes in the virtual setting, learn a search strategy or visual scan, formulate an action plan, inhibit automatic responses, inhibit distractors to the task (such as noises or irrelevant stimuli for the execution of the activity), increase the maintenance of attention, monitor the activity and the steps taken, predict the consequences of actions, consider alternatives, etc. An example of the tasks is shown in Figure 2.

The MRehab tool allows one to establish five levels of difficulty. Before starting the intervention program, a database will be created with each participant, assigning each of the tasks designed for each child according to the results of the previous assessment.

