1	Do you know the emotions?	Emotional perception	In the virtual school environment, children must identify the emotions on the faces of different children and adults.	Figure selection	Inhibitory control Working memory Flexibility	This activity consists in the selection of geometric figures that will appear on the left/right or top/bottom of the screen. The figures are organized in pairs, and the objective is to select the correct item from the appearance or disappearance of a signal. In the first two levels, an arrow indicates which option is correct. In the third and fourth levels, pairs of arrows will initially appear, one of which will then disappear, with the remaining one indicating the correct answer. In the fifth level, the signal will be a colored star (red or green), which will indicate the option to select. Finally, at level 6, the mechanism is similar to that of the third and fourth levels, that is, pairs of stars of different colors (red and green) will appear, of which one will disappear, with the color of the remaining one indicating the correct answer of the two options
2	Match and differences	Emotional perception Theory of Mind	Different family scenarios are presented at school and children are asked to identify the emotions on the faces and those shown by the body, in order to stimulate mentalization. What is this child thinking? How does the child feel? Do you choose a similar emotion in these two scenarios? Do you select contexts and situations where you can feel the same way?	Select equal and opposite emotions	Inhibitory control Working memory Flexibility	This activity is similar to the previous one, with the exception that this one is focused on emotions.

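### Virtual-task time and errors are to be tested across sessions, but each task is scheduled in one session only, so task differences and progress cannot be separated

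*Protocol article*

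**What the plan says.** - **Planned test.** Section 2.4.2 (Data Analysis Plan) lists, among the quantities whose differences will be tested for significance, "completion time and number of errors of each virtual task throughout the different sessions". The tests named are "Student’s t test, Mann–Whitney U-test, ANOVA or Kruskal–Wallis test", chosen by normality. The next sentence adds an effect size for the changes observed.
- **Data.** Section 2.2.1 (Study Variables) says the system will record, in each session and for each task, "number of hits, cognitive errors, and the time required by each participant to complete the task".
- **Schedule.** Section 2.2.3 (Experimental Group) sets 10 weekly sessions, "performing a task of each block per session", the blocks being emotional and cognitive regulation. Table 2 names the two tasks of every session.
- **Nearest thing to a repeat.** The session 2 cognitive task in Table 2 is described so: "This activity is similar to the previous one, with the exception that this one is focused on emotions".
- **Difficulty.** Section 2.2.3 states "The MRehab tool allows one to establish five levels of difficulty" and then describes a database built before the intervention, "assigning each of the tasks designed for each child according to the results of the previous assessment". Table 2, session 1, goes further for figure selection: "Finally, at level 6, the mechanism is similar to that of the third and fourth levels".
- **Control arm.** Section 2.2.3 (Control Group) says these children do similar activities without the virtual reality system.

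**The concern.** Testing a task's time and errors over sessions presupposes that the task comes back. Under Table 2 it does not. The child meets a different game each week, and the games differ in kind and length: paired-figure selection in session 1, Simon says in session 4, a collage in session 6, recall of animals after a 30 s display in session 7, a 10-stage check-in in session 10. Longer times or more errors in a later session may mean only that the later game is longer or harder.

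At stake is how the performance logs are read. Section 2.2.3 says they are kept for further analysis of the child's performance. A significant session difference, reported with an effect size, would naturally be presented as learning or as deterioration, and the design could support neither.

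**Working it through.** The plan gives no figure for this analysis, so there is none to reproduce. The check has three steps.

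**1. Does any task recur?** Table 2 has 10 sessions × 2 blocks = 20 task slots. Reading down the titles gives 10 different emotional and 10 different cognitive tasks, so 20 distinct tasks, each used once. Tasks seen in more than one session: 0 of 20. The session 2 cognitive task resembles that of session 1 but changes the content. Sessions 3 and 6 share the traffic-light idea, but one is a cognitive task on impulsive behaviour and the other an emotional task.

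**2. Can progress be identified?** Within one block, let the expected result of child *i* in session *s* be

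E(y_is) = c_i + τ_s + π_s,

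where c_i is the child's level, τ_s the effect of the task used in session *s*, and π_s progress up to session *s*. Because each task belongs to one session, τ and π carry the same index. The difference between sessions *a* and *b* within a child is

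(τ_b − τ_a) + (π_b − π_a).

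Adding any quantity to each τ_s and subtracting it from the matching π_s leaves every expected value unchanged, so only the sum can be estimated.

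The design matrix shows the same thing. Assume 13 children in the experimental arm (half of the planned 26).
- Task and child effects: 10 + 13 − 1 = 22 independent columns; computed rank 22.
- Adding a linear session trend: computed rank still 22.

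The trend adds no information beyond the task effects. Averaging a session's two tasks does not help, since both are new each week.

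**3. How often would task differences alone look like change?** Simulation of 2,000 runs: 13 children, 10 sessions, **no true progress**, child SD 1, residual SD 1, two-sided 5% level. The between-task SD is an assumption, in residual-SD units; the documents give none.

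| Between-task SD | Within-child linear slope, one-sample t test | ANOVA across sessions, sessions treated as independent groups |
|---|---|---|
| 0 | 4% | 0.15% |
| 0.25 | 14% | 4% |
| 0.5 | 33% | 54% |
| 1.0 | 59% | 98% |

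The slope test is not one the plan names; ANOVA is. The 0.15% in the first row arises because that ANOVA counts variation between children as error although the same children are measured in every session. That is a separate weakness, and a correct repeated-measures model would not cure the aliasing in step 2.

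**The case against.** The strongest reply is that the analysis attacked is inferred. Section 2.4.2 gives one phrase in a list of variables and mentions no trend or learning curve. It could mean that each task's time and errors, wherever the task falls in the programme, are compared between children or subgroups. The named tests are for independent groups, which suits that reading, and under it session and task are not confounded. The modelling of exploratory logs may also be left to a fuller plan.

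Part of this stands: the phrase is not fully explicit. But the reference to the different sessions, followed by an effect size for observed changes, fits a comparison over sessions better. It cannot be a between-arm comparison, because control children have no virtual-task data. And a later analysis plan could drop the test but could not create a repeated task.

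A second reply is that, read literally, section 2.2.3 assigns tasks to each child, so children need not all meet the same task in the same week. That would loosen the aliasing only if task order varied between children. Table 2 gives a single fixed order and nothing describes another.

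The third reply stands in full: these logs are neither a primary nor a secondary outcome in section 2.2.4.

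**Conclusion.** The point holds as a limited one. Under the Table 2 schedule, session and task are completely aliased, so the planned across-session test cannot show progress. This rests on the across-session reading of section 2.4.2 and on the fixed order in Table 2, not on the simulated rates, which only illustrate the possible size.

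A reader might infer more than the documents support:
- **That a session trend reflects the task and not the child.** It mixes the two in unknown proportion.
- **That false significance is certain.** With ANOVA the simulated rate runs from under 1% to 98%, depending on an assumed between-task SD.
- **That difficulty is set for each child.** This is inferred from two adjacent sentences in section 2.2.3; the text says tasks are assigned. A level held constant within a child would disturb comparisons between children, not that child's own trend.
- **That feelings will be scored as right or wrong.** The Emotion-Meter, engine and Volcano tasks ask how the child feels, but section 2.2.1 speaks of cognitive errors and nothing says that self-ratings will be counted.
- **That these logs are the only data gathered during treatment.** Section 2.2.2 also collects a Smileyometer rating of each activity in each session.
- **That the trial's conclusion is at risk.** The primary and secondary between-arm comparisons do not use these data.

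The mismatch between five levels in section 2.2.3 and a sixth in Table 2 is real but separate; it is not evidence for the aliasing.

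**What to change.** 1. In section 2.4.2, remove the significance test of virtual-task time and errors across sessions. Report both descriptively for each task within its own session, and by difficulty level if levels differ between children. State that differences between sessions will not be read as learning. Cost: a change of wording.
2. Optional, if a learning measure is wanted: replay one existing scored task, for example figure selection, at the same fixed level in the first and last sessions, and compare only that task, paired within child. Cost: a few minutes of session time, arranged before the sessions begin. It would still lack a control comparator, so it could not separate the programme from the natural development that the Discussion names as a limitation.
3. Reconcile the number of difficulty levels in section 2.2.3 with that in Table 2, session 1, before levels enter any analysis. Cost: an editorial correction.
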